### Investigation sites

RE-DINO operates in six French centers, selected for their obstetrical practices (routine use of a second Propess®), wish to be involved, and employment of high-quality research and clinical staff. Each center performed an in-house feasibility study. At the beginning, we will include at least 12 patients per month, thus at least two per month per center, over 30 months in several hospitals/university hospitals: Limoges, Clermont–Ferrand, and Marseille University Hospitals and Brive, and Tulle Hospitals. Initially, Blois Hospital was an investigative center but due to the low number of inclusions the center was closed and replaced in the study by Chambéry Hospital.

Central ethical approval has been confirmed from the Committee for the Protection of Personne of Sud-Ouest Outre-Mer IV (ref approval no. CPP16–030-PP) and we started recruiting at other centers in the trial only after local ethical approval was obtained.

## Discussion

We seek to answer a major clinical question. An increase in the number of vaginal deliveries in the experimental group (treated via placement of a second Propess®) may indicate how to decrease the rising nationwide cesarean rate. In addition, vaginal delivery reduces the length of maternal hospitalization (3 days versus 5–6 days after a cesarean section), thereby lowering the costs of care borne by society.

Currently, the use of only one Propess® is authorized. Although many teams place a second Propess® if the first has no effect, no consensus, recommendations, or comparative data are available. We will deliver objective evidence that may contribute to the establishment of a national protocol and unification of obstetric practices.

## Trial status

At the time of writing, the protocol is on its ninth version. Recruitment into the trial began on 30 December 2016. At the time of study design, the expected recruitment duration was 30 months. However, due to slower-than-anticipated accrual, the recruitment period has been extended to January 2022. On 10/22/2019, 110 patients have been randomized.

A populated SPIRIT checklist is provided in Additional file 1.

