### Sample size calculation

The number of participants is based on the primary outcome calculation for a comparative superiority test. Based on a local retrospective study (55% vaginal delivery rate after Propess® and 70% after two Propess® placements and Syntocinon®) performed prior to that of Antonazzo [13], the 15% between-group difference indicates that to afford an 80% power to detect a specific difference at the 5% significance level (two-sided test), 176 patients per group are required in a two-group scenario (nQuery Advisor 7). As the rate of non-evaluable patients (early drop-out, violation of inclusion or exclusion criteria, lack of compliance, intercurrent illness, comedication which was not allowed by the protocol) is expected to be very low in this study due to the nature of the primary outcome (vaginal delivery), we believe that a total of 360 (180 per group) will be an adequate sample size for the study.

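### At the average accrual the protocol reports, recruitment to January 2022 would yield about 196–199 women, not the 360 on which the stated power rests

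*Protocol article*

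**What the plan says.** Four statements in the protocol article bear on this, all in its current text.

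- **Sample size calculation.** The assumed rates are "55% vaginal delivery rate after Propess® and 70% after two Propess® placements and Syntocinon", with 80% power and a two-sided 5% level. From these, "176 patients per group are required in a two-group scenario". A small allowance for non-evaluable patients follows: "we believe that a total of 360 (180 per group) will be an adequate sample size for the study".
- **Investigation sites.** The original pace was set out as "we will include at least 12 patients per month, thus at least two per month per center, over 30 months". Six centers take part. One was closed for low inclusions and another took its place.
- **Trial status, observed accrual.** Recruitment opened on 30 December 2016. "On 10/22/2019, 110 patients have been randomized".
- **Trial status, new end date.** The article says that "due to slower-than-anticipated accrual, the recruitment period has been extended to January 2022".

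The article gives no reduced target, revised monthly rate, accrual by period or opening date for the replacement center. It does not say whether the date or the target decides when recruitment ends.

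**The concern.** The original plan was coherent: 12 per month for 30 months is 360. The extension moves the end date, but no new rate is given to show that the later date leads to 360. The date therefore has to be tested against the accrual the article itself reports.

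At stake is what the primary comparison can show. If recruitment ended in January 2022 with a little over half the planned women, the trial would have roughly even odds, or slightly better, of detecting the 15-point difference it was designed for. With 80% still the only power on record, a non-significant result could be read as evidence that a second pessary brings no benefit, when the data would not support that reading.

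**Working it through.** **Inputs.** Rates 0.55 and 0.70, two-sided 5%, 80% power, 176 per group, 360 in total (Sample size calculation); 12 per month over 30 months (Investigation sites); start 30 December 2016, 110 randomized by 22 October 2019, end in January 2022 (Trial status). The day in January is not given, so both 1 and 31 January are used. One month is 30.4375 days.

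**1. The protocol's own figure.** With d = 0.15 and mean rate 0.625, the uncorrected size per group is

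n = [1.960·√(2·0.625·0.375) + 0.842·√(0.55·0.45 + 0.70·0.30)]² / d² = (1.342 + 0.569)² / 0.0225 = 162.3, rounded up to 163.

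The continuity correction gives n′ = (n/4)·[1 + √(1 + 4/(n·d))]² = 40.58 × (2.079)² = 175.4, rounded up to 176. The stated 176 is reproduced exactly.

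**2. Observed rate.** 30 December 2016 to 22 October 2019 is 1026 days, or 33.7 months. 110 / 33.7 = 3.26 per month, which is 27% of 12.

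**3. Time left.** From 22 October 2019 to 1 January 2022 is 802 days (26.3 months), and to 31 January 2022 is 832 days (27.3 months).

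**4. Projected total at the reported average.** 110 + 3.26 × 26.3 = 196, and 110 + 3.26 × 27.3 = 199. That is 98–100 per group, about 55% of 360.

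**5. Rate needed for 360.** 250 / 27.3 = 9.1 and 250 / 26.3 = 9.5 per month, or 2.8–2.9 times 3.26. For the bare 352 (2 × 176), 242 women remain, which needs 8.9–9.2 per month.

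**6. Date for 360 at the reported average.** 250 / 3.26 = 76.6 months after 22 October 2019, about March 2026.

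**7. Power at the projected size.** Uncorrected power is Φ[(d·√n − 1.342) / 0.676]. On the corrected basis, n is first replaced by n·[1 − 1/(n·d)]², which inverts the correction in step 1.

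| Per group | Continuity-corrected (basis of 176) | Uncorrected |
|---|---|---|
| 98 | 52% | 58% |
| 100 | 53% | 59% |
| 176 | 80% | 83% |
| 180 | 81% | 84% |

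**8. Sensitivity to an assumed rate from October 2019 on.** Except for the first row, these rates are assumptions.

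| Rate per month | Total by January 2022 | Corrected power | Uncorrected power |
|---|---|---|---|
| 3.26 (reported average) | 196–199 | 52–53% | 58–59% |
| 5 | 242–247 | 63–64% | 68% |
| 6 | 268–274 | 68–69% | 72–73% |
| 6.53 (double) | 282–288 | 70–71% | 74–75% |
| 8 | 321–329 | 76–77% | 80% |
| 9.1–9.5 | 360 | 81% | 84% |

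**The case against.** The strongest reply is that this is a forecast and not a contradiction. The 3.26 is an average over the whole period. Other centers started only after local ethical approval, so openings may have been staggered, and replacing a low recruiter can raise the rate without changing the number of centers. The required 9.1–9.5 per month is also below the pace first thought feasible. All of this stands: a faster recent rate cannot be excluded.

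It does not close the gap. Had the trial already been running at 9.1–9.5 per month in October 2019, all 110 women would have come from about the last 12 of the 33.7 months (110 / 9.5 = 11.6; 110 / 9.1 = 12.1). The one reported change is a single center. If the rest held their average, it would have to bring about 6 more women per month (9.1–9.5 less 3.26), against an average of 0.54 per center (3.26 / 6). Even a doubled rate leaves the total below 290.

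A reader might infer three stronger things, and the documents support none of them:

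- *The extension cannot deliver 360.* That holds only if the average rate persists.
- *The sample size calculation or the 80% is wrong.* The 176 reproduces exactly, and 80% is the correct design power at that size.
- *The trial will stop in January 2022 short of target.* The date appears in a status note, not as a closing rule. It has been moved once and could be moved again.

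It is also fair to say that 59% should not be set against 80% without comment. The first is uncorrected, whereas the 176 behind the second is continuity-corrected. The like-for-like figure is 52–53%.

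Finally, the Statistical analysis section already promises an odds ratio with its 95% confidence interval. That helps, but it does not say how a result from a trial closed early would be read.

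**Conclusion.** The point holds as a conditional mismatch between the revised end date and the target of 360 with 80% power. It is not an error in the sample size calculation. If the reported average continues and recruitment ends in January 2022, the shortfall is about 161–164 women (360 less 196–199). Meeting the target by that date requires a near-tripling for which the article offers no basis.

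The conclusion rests on constant accrual at the average, on January 2022 being the actual end of recruitment, and on the protocol's 55% and 70%. Accrual figures by period could narrow or remove the gap, but they are not in the article.

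**What to change.** State which of the two governs the end of recruitment, and make the other figures follow.

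- **(a) The target governs.** Say that recruitment ends at 360 and not on a calendar date, and replace January 2022 with a date derived from a stated accrual projection and its basis. At the reported average that date is about March 2026. If recent accrual by period supports an earlier date, give those figures.
- **(b) January 2022 governs.** Restate the expected total (about 200) and its power for 55% versus 70%, naming the method: about 52–53% continuity-corrected, to match the 176, or 58–59% uncorrected. State before any data are seen that a non-significant result below 360 will be reported as inconclusive, with its confidence interval, and not as absence of benefit.

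The cost is some restated figures and, under (b), one sentence on interpretation. Neither option needs women beyond the 360 already planned or a change of design. The downside is a later end date under (a) and a less favourable stated power under (b).

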## Data Availability

Not applicable.

## Abbreviations

ANSM: “Agence Nationale pour la Sécurité du Médicament et des Produits de Santé”
CEBIMER: Center for Epidemiology, Biostatistics and Research Methodology of the University Hospital of Limoges
CONSORT: Consolidated Standards of Reporting Trials
CPP: Committee for the Protection of Personnel
ECRF: Electronic case record form
PG: Prostaglandin
PGE2: Prostaglandin E2
PHRC-I: Interregional Clinical Research Hospital Protocol
SAES: Serious adverse events
SPIRIT: Recommendations for Interventional Trials
UVEC: Unit of vigilance of clinical trials (pharmacovigilance unit)
WG: Weeks of gestation
